### Randomization

Sites will be randomized to conditions using random number generators in the SAS (version 9.4; SAS Institute). To ensure equivalence across treatment conditions, we will stratify random assignment based on two factors: (1) clinic types (eg, TB-specific NGOs, dental clinics, and NGOs implementing general health programs); (2) size of clinics with respect to the numbers of health care providers and patients. Randomization will be conducted within clinic types and matched by clinics with similar sizes. We will check the balance of treatment assignment on these 2 factors to assess the result of the random assignment. The health care providers and patients will not be blinded to their intervention condition.

A parallel study design will be used [43]. This design is considered the gold standard in assessing unbiased treatment effects given that randomization helps mitigate bias from known and unknown confounders. After randomization, individuals in each arm will stay in their assigned condition for the duration of the study. A cluster parallel RCT has the advantage of preventing inadvertent exposure to intervention or cross-over, thus reducing the risk of contamination [43].

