### Data Collection and Analysis or Statistical Considerations

We will first examine the demographic characteristics of the intervention and control arms to verify that randomization has resulted in arms with similar baseline characteristics. Analyses will be based on intent-to-treat. To control for potential confounders identified in bivariate analyses, as well as variables of a priori clinical significance (SES, gender, age), we will regress the 6-month follow-up outcomes on the intervention status with the adjustment of baseline measures. We will use a regression model with a logit link function for binary outcomes (eg, tobacco cessation as our primary outcome), an identity link function for continuous outcomes (eg, number of cigarettes), and a Poisson link function for count outcomes (eg, number of attempts to quit). We will use robust standard error estimates (Generalized Estimating Equations method), adjusting for the clustering of patients among practitioners. We will conduct stratified analyses by clinic types to assess potential effect modification by settings. Independent variables with strong high correlations may result in collinearity. To assess the extent of collinearity, we will assess variance inflation factors and the standard error estimates for the adjusted model.

We will also measure the receipt of intervention using process data from the NSF team and conduct a dose-response analysis of the program impact. We will categorize patients in the intervention arm into 6 subgroups (brief advice, brief advice + intake, brief advice + intake + 1 follow-up, brief advice + intake + 2 follow-ups, etc). The mobile app will capture this information. While the study is not powered to detect differences between the subgroups definitively, we expect to be able to detect trends in response to the level of receipt of intervention, contingent on the distribution of exposure across subgroups.

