### Power Analysis and Sample Size

Our sample size estimates were calculated conservatively. Based on the estimates of a risk ratio of 1.75 and the proportion (3.72%) of the control arm who quit smoking (216/5811) in a recent meta-analysis of brief advice interventions [45], we calculated an estimated proportion (6.50%) of the intervention arm who received the brief tobacco intervention and quit tobacco use. We are conducting a cluster RCT with practice settings as the unit of random assignment. Assuming an intraclass correlation of 0.01 and the potential pool of practitioners to be 131, we will need about 36 tobacco-using patients for each practitioner to have a total sample size of 2344 tobacco users per arm, based on a type I error rate of 0.05 and 80% statistical power. Thus, our proposed final sample size is 4688, accounting for 20% attrition among practitioners and 30% among patients. Our effect size estimate is conservative in light of a recent study suggesting a 12.5% quit rate at 6 weeks among smokers receiving behavioral counseling in a pre-post comparison without a control arm receiving standard care in India [9]. Although the 6-month quit rate tends to be lower than the 6-week quit rate after brief advice, we expect our conservative sample size estimate should provide adequate statistical power.

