### Compensation Details

All study participants will receive small monetary incentives to express our appreciation for their participation. Practitioners will receive INR 500 (about US $6) for completing each of the following activities: attending training, registering each patient, completing a 3-month posttraining follow-up survey, and completing a 6-month posttraining follow-up survey. Patients will receive INR 500 (about US $6) when they register for the study, INR 200 (a little over US $2) for completing each of the 1-week, 1-month, and 3-month follow-ups, and INR 500 (about US $6) for completing the 6-month follow-up. The patients who undergo cotinine testing will also receive INR 500 (about US $6) for completing the test. Each of the health and TB NGO sites will receive a one-time payment of INR 10,000 (about US $120) per practitioner participating to account for overhead costs. Given that the dentist practitioners operate their own practices, they will not receive a site-level incentive. These amounts were selected based on the NSF team’s past experiences delivering similar programs to ensure that the amounts are enough to be meaningful to the study populations but not coercive.

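### Sites are randomised but the outcome GEE clusters only by practitioner, so type I error exceeds 5% if patients of different practitioners at a multi-practitioner NGO site have positively correlated outcomes

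*Protocol article*

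**What the plan says.** The unit of randomisation is stated twice. Under Randomization: "Sites will be randomized to conditions using random number generators". Under Power Analysis and Sample Size: "We are conducting a cluster RCT with practice settings as the unit of random assignment".

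The cluster level of the analysis is stated once, under Data Collection and Analysis or Statistical Considerations: "We will use robust standard error estimates (Generalized Estimating Equations method), adjusting for the clustering of patients among practitioners". It follows directly on the list of link functions for the 6-month outcomes, which includes the logit link for cessation as the primary outcome. No site-level cluster, random effect or variance is mentioned there or elsewhere.

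Two places show that site and practitioner need not coincide. One stratification factor is the "size of clinics with respect to the numbers of health care providers and patients". Under Compensation Details, "Each of the health and TB NGO sites will receive a one-time payment of INR 10,000 (about US $120) per practitioner participating". The same section suggests that the dental stratum is different: "Given that the dentist practitioners operate their own practices, they will not receive a site-level incentive".

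**The concern.** A sandwich variance allows for correlation inside the declared cluster and treats different clusters as independent. All practitioners at one site receive the same arm. If their patients' outcomes are also positively correlated, the site adds variance to the arm comparison that a practitioner-clustered variance does not see. The primary p-value and confidence interval would then be too optimistic, and a programme without effect would be declared effective in more than 5% of such trials.

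This is a stated rule, set below the level of randomisation, and not a detail left open for the SAP. An SAP that followed the sentence would carry it forward.

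**Working it through.** **1. Which cluster the sample size uses.** Inputs from Power Analysis and Sample Size: control quit rate 3.72%, intervention quit rate 6.50%, 80% power, ICC 0.01, about 36 patients per practitioner, attrition of 20% (practitioners) and 30% (patients). Type I error is 0.05; two-sided testing is my assumption, as the article does not say.

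- Two proportions without clustering: 984 per arm.
- Design effect with the practitioner as cluster: 1 + (36 − 1) × 0.01 = 1.35.
- Attrition factor: 0.7 × 0.8 = 0.56.
- 984 × 1.35 / 0.56 = 2372 per arm, against the stated 2344 (+1.2%).

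If the ICC of 0.01 applied to whole sites with two practitioners each, the design effect would be 1 + (72 − 1) × 0.01 = 1.71 and the result 3005. The stated figure therefore fits the practitioner as cluster, which agrees with the analysis section.

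**2. Inputs for the type I error.**

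- m = 36 × 0.7 = 25.2 analysed patients per practitioner (from the article).
- ρp = 0.01, the ICC within a practitioner. The article does not name the level of its ICC; step 1 reads it as practitioner level.
- k, practitioners per NGO site: not given. Assumed 2, 3, 5, 10.
- ρs, the ICC between patients of different practitioners at one site: not given. Assumed 0, 0.0025, 0.005, 0.01. The last equals ρp and is a ceiling, since it leaves practitioners no clustering of their own.
- f, the share of practitioners in multi-practitioner NGO sites: not given. Assumed 2/3, with the other third in single-dentist sites.

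**3. Formulas.**

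- Variance factor that practitioner clustering captures: Vp = 1 + (m − 1)ρp = 1 + 24.2 × 0.01 = 1.242.
- True variance factor: V = Vp + f(k − 1)mρs.
- Actual two-sided type I error: 2 × [1 − Φ(1.96 / √(V/Vp))].

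Example with k = 5, ρs = 0.005: V = 1.242 + (2/3) × 4 × 25.2 × 0.005 = 1.242 + 0.336 = 1.578. The ratio is 1.271 and 1.96/√1.271 = 1.739, which gives 8.2%.

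**4. Results, mixed setting (f = 2/3).**

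| k in NGO sites | ρs = 0 | 0.0025 | 0.005 | 0.01 |
|---|---|---|---|---|
| 2 | 5.0% | 5.4% | 5.8% | 6.6% |
| 3 | 5.0% | 5.8% | 6.6% | 8.2% |
| 5 | 5.0% | 6.6% | 8.2% | 11.4% |
| 10 | 5.0% | 8.6% | 12.2% | 18.8% |

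If every site had k practitioners (f = 1), the ceiling ρs = 0.01 would give 7.4%, 9.8%, 14.5% and 24.4%. That case leaves out single-dentist sites and bounds the table from above.

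**5. Check by simulation.** Null trials, 20,000 per scenario, about 130 to 140 practitioners, 25 patients each, quit rate 5%, robust logit Wald test, f = 1, ρp = 0.01:

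| k | Sites | By practitioner, ρs = 0 | By practitioner, 0.005 | By practitioner, 0.01 | By site, uncorrected, 0.01 |
|---|---|---|---|---|---|
| 2 | 66 | 5.5% | 6.2% | 7.7% | 5.7% |
| 3 | 44 | 5.2% | 8.1% | 10.3% | 6.4% |
| 5 | 26 | 5.4% | 10.5% | 14.9% | 7.4% |
| 10 | 14 | 5.2% | 16.8% | 25.3% | 9.9% |

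The formula is confirmed: at f = 1 and ρs = 0.005 it gives 6.2%, 7.4%, 9.8% and 15.6%. Without correlation between practitioners there is no inflation beyond the slight excess also seen with one practitioner per site (5.3% to 5.5%). Clustering by site removes most of the inflation. What remains is small-sample bias of the uncorrected sandwich, which grows as sites become fewer.

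**The case against.** A reader might infer that the test is invalid at every site with more than one practitioner. The article does not support that. Inflation also needs positive correlation between patients of different practitioners; at zero correlation the test keeps its level whatever the number of practitioners. That objection stands, and the finding is conditional on it.

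A reader might also take 14.5% or 24.4% as the expected error. Those figures assume five or ten practitioners at every site and the ceiling correlation. The article gives no practitioner count per site, and since dentists run their own practices, that stratum probably contributes little or nothing. NGO practitioners are outreach or community health workers who may cover different areas, and counselling comes by telephone from the foundation's staff. The correlation may therefore be small. This also stands.

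Randomisation within clinic type, matched on size, and adjustment for baseline measures, SES, gender and age can remove part of the between-site variance. Practitioner attrition would lower the number per site. The formula ignores both, so it tends to overstate. Neither makes the practitioner the right cluster, because site variance that remains is still unseen.

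Finally, the article condenses a fuller protocol, which might nest practitioners within sites. But the article does name a level, and it is below the randomised one. This objection does not remove the point.

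**Conclusion.** The point holds in conditional form. The article states the randomised unit and the analysis cluster plainly, and they differ. Validity of the primary test then rests on an unstated assumption: no correlation between patients of different practitioners at the same NGO site.

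The mismatch is certain; its size is not. In the five-practitioner mixed scenario the type I error runs from 5.0% to 11.4% as the between-practitioner ICC goes from 0 to 0.01. With two practitioners per NGO site it stays between 5.0% and 6.6%. The inflation would come mainly from the general-health and TB NGO strata. It should be corrected before analysis because it bears on the primary p-value and interval and the remedy is cheap.

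**What to change.** In Data Collection and Analysis or Statistical Considerations, replace the practitioner with the randomised site as the GEE cluster for all patient outcome models; practitioner may be nested within site but should not be the top level. In the same sentence, specify a small-sample corrected sandwich variance with a t reference. A changed cluster identifier alone is not enough: uncorrected site clustering still rejected 6.4% with 44 sites and 7.4% with 26 in the simulation. Stating the number of sites and practitioners per site by stratum would let readers judge how much this matters.

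Cost: one sentence, a different cluster identifier in the code, and somewhat wider intervals. No new data are needed as long as the site of each practitioner is on file, which site randomisation already requires.

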### Theoretical Framework

The objective of this study is to test the effect of an adapted EBI, LifeFirst SWASTH, compared to receiving a pamphlet about the health effects of tobacco use, on improving cessation rates among tobacco users in 3 types of low-resource, high-reach health care settings in Mumbai: NGOs implementing general health programs, TB-specific NGOs, and dental clinics. This Hybrid Randomized Control Trial Type 1 study [41] will evaluate program effectiveness and explore the implementation of LifeFirst SWASTH, drawing on the US Public Health Service 5A’s model of tobacco control [42] and the Exploration, Preparation, Implementation Sustainment framework [24]. Figure 1 details the study’s theoretical framework. We hypothesize that 30-day point prevalence abstinence (PPA) will increase, and tobacco use will decrease at 6-month follow-up among patients in the adapted EBI, LifeFirst SWASTH, arm compared to the patients in the control arm.

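### Stratified analyses by clinic type do not by themselves test whether the effect differs between settings, and the protocol states no formal comparison of the three results

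*Protocol article*

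**What the plan says.** The section on data collection and analysis gives one sentence to this question: "We will conduct stratified analyses by clinic types to assess potential effect modification by settings". It states a purpose (effect modification) and a method (stratified analyses). The article names no arm-by-setting interaction, no heterogeneity test and no rule for comparing the stratum results.

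The settings are the "3 types of low-resource, high-reach health care settings in Mumbai: NGOs implementing general health programs, TB-specific NGOs, and dental clinics". Clinic type is also a randomization factor: "Randomization will be conducted within clinic types and matched by clinics with similar sizes".

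The main analysis of the binary outcome is a logit model fitted by GEE with robust standard errors, clustered on practitioner. The sample size is set for the pooled comparison of the two arms. The one warning about limited power in the analysis section concerns the dose-response subgroups, not the settings.

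**The concern.** Effect modification is a statement about the difference between effects. Three separate models give three estimates, each with its own interval and p-value, and none of these measures the difference between settings. One significant and one non-significant setting is not evidence that the two differ, least of all when each setting has low power.

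At stake is a conclusion that the program works in one type of setting and not in another when the data do not support it. Aim 2 covers all three settings and the article argues for wider scale-up, so such a statement could influence where the program is offered. The direct test needs nothing new: clinic type is recorded, was used in randomization, and can enter the planned GEE model.

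**Working it through.** **Inputs** (Power Analysis and Sample Size section, unless marked as assumed)
- Quit proportions: control 3.72%; "an estimated proportion (6.50%) of the intervention arm". Difference 0.0278, mean 0.0511.
- Design: "based on a type I error rate of 0.05 and 80% statistical power". Sidedness is not stated; two-sided is assumed.
- Clustering: "Assuming an intraclass correlation of 0.01 and the potential pool of practitioners to be 131", with about 36 patients per practitioner.
- Size: 2344 per arm, with 20% attrition of practitioners and 30% of patients, so retention is 0.8 × 0.7 = 0.56.
- Assumed: equal thirds of patients per setting, and the same ICC in each setting.

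**Step 1: reproduce the plan's figure**

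n per arm = [1.96·√(2·0.0511·0.9489) + 0.842·√(0.0372·0.9628 + 0.065·0.935)]² / 0.0278² = 984.

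Design effect = 1 + (36 − 1) × 0.01 = 1.35. Then 984 × 1.35 = 1328, and 1328 / 0.56 ≈ 2372 per arm, against 2344 stated (1.2% apart). Forward check: 2344 × 0.56 / 1.35 = 972 effective patients per arm, with overall power 0.795. The inputs are therefore read as the plan intends.

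**Step 2: power within one setting**

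Analysed per arm: 2344 × 0.56 = 1313. Power = Φ[(0.0278 − 1.96·SE₀)/SE₁], where SE₀ uses the pooled variance and SE₁ the unpooled variance.

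| Patients per practitioner | Design effect | Effective n per arm per setting | SE₀ | SE₁ | Power |
|---|---|---|---|---|---|
| 36 | 1.35 | 1313/1.35/3 = 324 | 0.01730 | 0.01726 | 0.362 |
| 36 × 0.7 = 25.2 | 1.242 | 1313/1.242/3 = 352 | 0.01659 | 0.01656 | 0.388 |

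**Step 3: pattern of significance under an identical effect**

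The settings are independent, so P(mixed) = 1 − P(all significant) − P(none significant).
- Power 0.362: all 0.362³ = 0.047; none 0.638³ = 0.260; mixed 0.693.
- Power 0.388: all 0.058; none 0.229; mixed 0.712.

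**Step 4: sensitivity of P(mixed)**

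| Retention and patients per practitioner | Equal thirds | 50/25/25 | 60/20/20 |
|---|---|---|---|
| 0.56, 36 | 0.693 | 0.705 | 0.722 |
| 0.56, 25.2 | 0.712 | 0.726 | 0.745 |
| 0.70, 25.2 | 0.746 | 0.767 | 0.794 |
| 1.00, 36 | 0.733 | 0.768 | 0.812 |

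The range is 69–77% for the first two splits and reaches 81% for the most uneven one. Simulation with tests on the log odds ratio (200,000 runs; equal thirds and 50/25/25) gives 67–77%.

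**Step 5: other ways of reading the same results**

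These come from the same kind of simulation, with an identical effect in all settings.
- Joint heterogeneity test (Cochran's Q, 2 df, 0.05): false signal in 3.8–4.5% of runs; nominal 5%.
- Declaring a difference only if two settings' 95% intervals do not overlap: about 1% (equal thirds, 0.56 retention).
- Comparing point estimates by eye: the median ratio of the largest to the smallest setting odds ratio is about 1.55–1.85.

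Power of the joint test when settings truly differ (risk ratios 1.0, 1.75 and 2.5; equal thirds; 0.56 retention): about 35% at design effect 1.242 and 32% at 1.35.

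**The case against.** A reader might infer that the plan, followed as written, will probably report a setting difference that does not exist. The article does not support that. It never says that settings will be compared by which stratum reaches p<0.05 and does not mention within-setting p-values. Stratified estimates are a standard first step and can be read through their confidence intervals. The same output leads to a false difference about 1% or about 70% of the time, depending on a reading rule that the article leaves open. This objection stands, so the 70% belongs to one reading only.

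Two further limits also stand. The 4–5% for the joint test assumes that practitioner-level clustering is adequate, whereas sites are the unit of randomization and their number is not given. And the analysis is ancillary: no aim or hypothesis concerns differences between settings, and each stratum is itself a randomized comparison.

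It can also be said that a one-sentence summary leaves the formal test to a fuller document. That carries less weight here, because the sentence does more than stay silent: it names stratified analysis as the means of assessing effect modification. It does not, however, exclude an added test.

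**Conclusion.** The point holds in a limited form. The method named does not by itself answer the question named, and no formal comparison is stated. If the strata were read by significance, a mix of significant and non-significant settings would arise about 70% of the time under an identical effect, against about 4–5% false signals for a joint test. The comparison rests on the plan's own quit rates, ICC and attrition, a two-sided test, a common ICC, and a patient split that the article does not give; the result changes little with that split. The documents do not show that the sponsor intends such a reading. The primary comparison of the arms is untouched, so this is a worthwhile low-cost improvement and not a threat to the main result.

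**What to change.** Replace the sentence in the analysis section with text to this effect:

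*Effect modification by setting will be assessed by an arm-by-clinic-type interaction (2 df) in the primary GEE logit model, with clinic type as a main effect. Setting-specific effects with 95% confidence intervals will be reported as exploratory. Within-setting p-values will not be used to claim a difference between settings.*

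The cost is a few sentences and one added model term, with no new data. The drawback is the interaction test's low power, so the text should add that a non-significant interaction does not show equal effects. The setting-specific estimates remain available to readers either way.

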### Intervention Arm

In LifeFirst SWASTH, patients who use tobacco will receive a pamphlet in Hindi about the harmful effects of tobacco. Practitioners will be trained to deliver the brief advice intervention. They will use an app to facilitate ongoing engagement and learning related to the adapted brief advice intervention. The app offers:

(1) a system to document patients’ tobacco use and refer them to LifeFirst SWASTH for counseling; (2) a dashboard allowing them to follow the progress of the patients they have referred; and (3) a repository of training materials and additional resources, for example, support material for promoting cessation, and quiz questions to test their knowledge.

An NSF-moderated group chat in the popular social media channel, WhatsApp, will also be used as a forum to share practitioners’ innovations and successes.

Within 15 days of referral, patients will be contacted by a trained NSF counselor over the telephone, given more details about the study, and asked whether they would like to provide informed consent and participate. The counselors will follow up with the patients for a total period of 6 months, with 4 specific follow-up intervals at 1 week, 1 month, 3 months, and 6 months after the initial detailed counseling call to ask about tobacco use and provide continued support.

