### Primary Outcome: Intervention Effectiveness

The primary outcome is a 30-day PPA from tobacco. Twenty percent of those who self-report tobacco cessation 6 months post recruitment will receive a cotinine test (using a urine sample) to biochemically verify abstinence.

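### The planned dose-response analysis counts the 6-month call as dose although that call also supplies the outcome, so dose level determines whether an outcome is observed

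*Protocol article*

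**What the plan says.** The section *Data Collection and Analysis or Statistical Considerations* of the protocol article plans to "conduct a dose-response analysis of the program impact". It states: "We will categorize patients in the intervention arm into 6 subgroups". The levels begin with brief advice and brief advice plus intake, and continue as "brief advice + intake + 1 follow-up, brief advice + intake + 2 follow-ups, etc".

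The section *Intervention Arm* schedules the counsellor's contacts "with 4 specific follow-up intervals at 1 week, 1 month, 3 months, and 6 months after the initial detailed counseling call". The purpose of each is "to ask about tobacco use and provide continued support", so measurement and support happen in the same call.

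The outcome is set at the last of these contacts. The analysis section says "we will regress the 6-month follow-up outcomes on the intervention status with the adjustment of baseline measures". Under *Primary Outcome: Intervention Effectiveness*, "Twenty percent of those who self-report tobacco cessation 6 months post recruitment will receive a cotinine test", and *Informed Consent* places the arrangement of that test after the 6-month call. The article names no other source of a 6-month outcome for a patient who misses that call.

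Analyses are to follow intent-to-treat. The article gives no rule for missing 6-month outcomes.

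**The concern.** A dose-response analysis asks whether patients who received more of the programme did better. It needs an exposure that is fixed before the outcome and does not decide whether the outcome is seen. Here the last exposure step and the outcome measurement are one event, so a patient who takes the 6-month call gains one dose level and an outcome together.

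The comparison is also not randomised, because patients end up at a level by taking or missing calls. Yet the article describes the analysis in terms of programme impact and expects to detect trends with the level of receipt. A gradient produced by who was measured could be read as supporting evidence that counselling works.

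**Working it through.** **Step 1: is the 6-month call in the dose?** The listed levels give 1 (advice) + 1 (intake) + *k* (follow-ups) = 6, so *k* = 4. The schedule has exactly four follow-ups, the fourth at 6 months. A scale with a no-contact level and only three calls would also have six levels, but the list starts at brief advice. The article's own count of six therefore reproduces only with the 6-month call included.

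**Step 2: who has an outcome?** Advice only and advice plus intake mean no follow-up calls, hence no 6-month call and no outcome. Four calls means the 6-month call took place. Patients with one to three calls have an outcome only if the 6-month call was among them.

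**Step 3: inputs.** Completion rates come from *Results*, both arms pooled:
- *p*1 = 1460/1574 = 0.9276
- *p*2 = 1089/1204 = 0.9045
- *p*3 = 583/667 = 0.8741
- *p*4 = 188/248 = 0.7581

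The no-effect quit rate from *Power Analysis and Sample Size* is 216/5811 = 3.72%. Assumptions: calls are missed independently, all patients have intake, the pooled rates apply to the intervention arm, and quitting is unrelated to the number of calls.

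**Step 4: share with an outcome.** Let *m*(j) be the probability of completing j of the first three calls: *m*(0) = 0.00087, *m*(1) = 0.02545, *m*(2) = 0.24036, *m*(3) = 0.73332. For k = 1 to 3,

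share(k) = *p*4·*m*(k−1) / [*p*4·*m*(k−1) + (1−*p*4)·*m*(k)]

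For example, share(2) = 0.7581×0.02545 / (0.7581×0.02545 + 0.2419×0.24036) = 0.01930/0.07745 = 24.9%.

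If missing is scored as use, the apparent quit rate is share × 3.72%.

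| Follow-up calls | Expected patients of 2344 | With 6-month outcome | Apparent quit rate, missing = use | Quit rate, responders only |
|---|---|---|---|---|
| 0 | 0.5 | 0% | 0% | none observed |
| 1 | 16 | 9.7% | 0.36% | 3.72% |
| 2 | 182 | 24.9% | 0.93% | 3.72% |
| 3 | 843 | 50.7% | 1.88% | 3.72% |
| 4 | 1303 | 100% | 3.72% | 3.72% |

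**Step 5: the trend test under this null.** In 1000 simulated intervention arms of 2344 patients, clustering ignored, a Cochran-Armitage test at nominal 5% gave:
- Missing = use, independent calls: rejection in 91% of runs.
- Missing = use, monotone dropout (a missed call means no later calls): rejection in 100%.
- Responders only, independent calls: rejection in about 5%, as it should be.
- Responders only, monotone dropout: not estimable, because every responder is at the top level.

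**Step 6: is removing the 6-month call from the dose enough?** No. Among responders it subtracts one call from everyone and leaves the trend test unchanged. If missing is still scored as use and dropout is monotone, patients with fewer than three earlier calls all score 0%. Those with three score 0.7581/0.8741 × 3.72% = 3.22%. The dose definition and the missing-outcome rule must change together.

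**The case against.** The strongest reply is that the false trend needs a rule the article does not contain. Intent-to-treat does not by itself mean that missing counts as use, and the rule may stand in an SAP that is not at hand. This stands. A reader might infer that a dose-response will appear even if the programme does nothing. The documents do not support that, since among responders the rates are flat or no trend can be estimated. The dose definition does not depend on that rule, however. An SAP could not leave the 6-month call out of the scale without departing from the article's six levels.

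Second, the article already says that the study is not powered for definitive subgroup differences and that trends depend on how exposure is distributed. Its limitations mention loss to follow-up and selection bias in general. These caveats are fair, but they concern precision and the trial as a whole. They do not address an exposure that includes the outcome measurement, and a larger sample would only make an artefact more significant.

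Two further readings should be resisted. One is that patients who keep taking calls are those doing well. The article gives no data on this and pays patients for each completed follow-up, which is a reason to answer whatever their tobacco status. The direction of any selection is unknown. The other is to illustrate a null programme with a 6.5% quit rate, which makes the gradient steeper. That is the plan's expected rate with the intervention; its no-effect rate is 3.72%.

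**Conclusion.** The concern holds in a conditional form. That the six-level scale includes the outcome call, and that its two lowest levels can have no observed outcome, follows from the text without assumptions. The consequence depends on how missing outcomes are handled. Scoring them as use produces a spurious rise from about 0.4% at one call to 3.7% at four. Restricting to responders produces no mechanical trend, but the six-level analysis cannot be carried out as described. Imputation would not create the artefact mechanically, but every outcome in the two lowest levels would be imputed.

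The size of the gradient rests on independent call completion and on interim rates; the 6-month rate comes from only 248 eligible patients. Under monotone dropout the pattern is a step from 0% to 3.72% at the top level. Confounding by engagement is a separate matter and was not quantified. The analysis is supplementary and within one arm, so this should be corrected but does not threaten the trial's main result.

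**What to change.** 1. Define dose only from contacts before the 6-month assessment: advice, intake, and the 1-week, 1-month and 3-month calls (five levels).
2. For this analysis, do not score missing 6-month outcomes as tobacco use. Analyse patients with an observed 6-month outcome, use weighting or imputation as a sensitivity analysis, and report how many at each level have an outcome.
3. Describe the result as a non-randomised, adjusted association rather than as programme impact.

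The cost is some wording and a few lines of code, with no new data. The downside is sparse lower levels. On the assumptions above, about 1777 of 2344 patients (0.7581 × 2344) would have an outcome: roughly 2, 45, 427 and 1303 with intake and zero, one, two and three earlier calls. Advice only may well stay empty, because the calls are timed from the initial counselling call. Under monotone dropout no trend could be estimated, and the report should then say so.

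Two additions that may suggest themselves are not advised. The control arm's call-completion gradient is a poor benchmark, because control patients who ask for counselling are withdrawn and classed as lost to follow-up. Arm assignment is not a clean instrument for counselling, because it also brings practitioner training and brief advice.
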